## Abstract

**Background:**

The proportion of pregnant women who have a caesarean section shows a wide variation across Europe, and concern exists that these proportions are increasing. Much of the increase in caesarean sections in recent years is due to a cascade effect in which a woman who has had one caesarean section is much more likely to have one again if she has another baby. In some places, it has become common practice for a woman who has had a caesarean section to have this procedure again as a matter of routine. The alternative, vaginal birth after caesarean (VBAC), which has been widely recommended, results in fewer undesired results or complications and is the preferred option for most women. However, VBAC rates in some countries are much lower than in other countries.

**Methods/Design:**

The OptiBIRTH trial uses a cluster randomised design to test a specially developed approach to try to improve the VBAC rate. It will attempt to increase VBAC rates from 25 % to 40 % through increased women-centred care and women’s involvement in their care. Sixteen hospitals in Germany, Ireland and Italy agreed to join the study, and each hospital was randomly allocated to be either an intervention or a control site.

**Discussion:**

If the OptiBIRTH intervention succeeds in increasing VBAC rates, its application across Europe might avoid the 160,000 unnecessary caesarean sections that occur every year at an extra direct annual cost of more than €150 million.

**Trial registration:**

Current Controlled Trials ISRCTN10612254, registered 3 April 2013.

## Background

Concern has been expressed globally at the rising caesarean section rate. For example, the World Health Organization (WHO) recently noted that ‘caesarean section rates higher than 10 % are not associated with reductions in maternal and new-born mortality rates’ [38]. In the United States in 2012, the caesarean section rate rose for the twelfth consecutive year to 32.8 %, a proportional increase of 56 % since 1996 [24]. In Europe, the caesarean section rate increased between 1999 and 2005 in all European Union member countries for which data were available [5]. In 2010, Italy had a caesarean section rate of 38 %, whereas the rate was 17 % in the Netherlands, indicating wide variations in maternity care practices within Europe [12, 23]. Some of the reasons that have been offered for the continuing increase in caesarean sections include medico-legal issues, the increasing use of electronic foetal heart rate monitoring, and reduced training in operative vaginal and vaginal breech births [1, 2, 19]. Maternal request for caesarean section, that is, a caesarean section in the absence of medically indicated reasons, is a further frequently cited reason for increasing caesarean section rates, ranging from 2.6 % to 26.8 % of all caesarean sections [20, 32]. The most common reason, however, is repeat caesarean section following previous caesarean section [27], and this is a significant factor contributing to the overall increased caesarean section rates. Repeat caesarean section accounts for more than one-third of all caesarean sections in the United States [7].

Vaginal birth after caesarean (VBAC) is a safe alternative to repeat caesarean section, is preferred by most women and is deemed to be a key way of reducing overall caesarean section rates (Cunningham 2010). However, VBAC rates, which rose steadily across the world in the early 1990s, have declined dramatically again. In 2006, for example, approximately 8 % of women in the US who had a previous caesarean section had a VBAC in their next pregnancy (Cunningham 2010). Other reports indicate VBAC rates of between 30 % and 56 % [4, 37]. In Europe, wide variations in VBAC rates exist between and within countries, reflecting variations in maternity care practices and maternity care provision. For example, VBAC rates in Germany, Ireland and Italy have been found to be significantly lower (29 to 36 %) than those in the Netherlands, Sweden and Finland (45 to 55 %) [11]. Combined with the high caesarean section rates in some countries, such as Italy, this means that many women in Europe are unlikely to have a vaginal birth unless they indicate that they would prefer that over a caesarean section [10].

A number of reasons are offered for the variations in VBAC rates. These include medico-legal factors and the inaccessibility of tertiary care centres, but variations in caesarean section rates are more likely to reflect national and individual clinician’s approaches to clinical decision-making [18]. Of the women who do choose and are supported to have a planned VBAC, VBAC success is considerably higher (70 % to 87 %) than the average rates (Cunningham 2010, [13]). This indicates that VBAC is a real and viable option for most women with previous caesarean section.

Increasing the caesarean section rates in conjunction with declining VBAC rates is a maternity care issue of particular concern. If caesarean section rates continue to rise at the rate of recent years, the projected overall caesarean section rate by 2020 will be 56 % [36]. Considering the increased adverse maternal and neonatal outcomes associated with caesarean section [9, 15–17, 21, 25, 28, 37], this trend and its potential effects on the health of women and babies into the future requires more attention. A dedicated and concerted effort by women and clinicians has the potential to halt increasing caesarean section rates [3], increase VBAC rates [33] and improve the overall maternal and neonatal health and wellbeing of women and their babies.

The OptiBIRTH trial, conducted across different European health settings, involves unique collaborative efforts of women and clinicians. It seeks to enhance women-centred maternity care and, through the development and testing of an innovative complex intervention aimed at increasing VBAC rates in high caesarean section and low VBAC countries, reduce the fragmentation and lack of coherence in health service delivery. The OptiBIRTH trial will provide evidence to inform the organisation and provision of maternity care for many hundreds of thousands of women with previous caesarean section in Europe. Two systematic reviews of existing evidence have been published as part of the wider OptiBIRTH project: one on women-centred interventions and one on clinician-centred interventions for increasing VABC rates [22, 30]. These provide justification for this trial and assisted in the design of the OptiBIRTH intervention.

This protocol sets out the design of the OptiBIRTH trial and has been prepared in accordance with the SPIRIT guidelines for the protocol for a randomised trial [6]. Findings of the trial will be reported in accordance with the CONSORT recommendations [26].

### Aim

The aim of the OptiBIRTH project, of which this trial is one component, is to improve maternal health service delivery, and optimise childbirth by increasing vaginal birth after caesarean section through enhanced women-centred maternity care across Europe.

### Objectives

The objective of this trial is to compare the effects of an intervention that has been developed with the intention of maximising VBAC versus usual care. This will be done through a cluster randomised trial in maternity units in three European countries with relatively low VBAC rates. The intervention was developed within the OptiBIRTH project and includes an effort to develop communities of practice in the intervention sites through face-to-face and online activities.

### Registration

The OptiBIRTH trial was prospectively registered in the ISRCTN Registry before randomisation was done (ISRCTN applied for: 17 March 2013; ISRCTN assigned: 3 April 2013; and randomisation conducted: 7 April 2013). The trial was assigned the following number: ISRCTN10612254.

### Study setting

A total of 16 sites (maternity units) agreed to take part in the OptiBIRTH trial initially: five from Ireland, five from Italy and six from Germany. In order to be eligible for participation, each site had to have a VBAC rate of less than 35 % and to provide a letter from the lead obstetrician (and, when available, the lead midwife) stating that they were willing for their institution to join the study. However, one of the German sites was withdrawn from the trial because of failure to recruit any participants in the first 6 months.

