## Methods/Design

### Design

This is a cluster randomised trial of maternity units in three countries with relatively low VBAC rates (Germany, Ireland and Italy). The units represent a variety of healthcare settings (small, medium and large units, with annual births of 2,000 to 8,500) in both urban and rural locations [14]. For the purposes of the randomisation, two maternity units in the same city in Germany were considered as a single cluster for the purposes of the trial.

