### Randomisation

The unit of randomisation in the trial is the maternity unit (the ‘site’). Randomisation had to be done in advance of recruiting women to participate in the trial to allow appropriate preparations to be made in each site. Further, given the temporal nature of pregnancy, it is not possible to hold randomisation until all women in each participating site have been recruited, because some women would have given birth by the time the last woman would have been recruited. However, as with cluster trials in which the participants cannot be blinded to the intervention, once the sites had been randomised, it is possible that recruitment of women to the trial was influenced by the knowledge of whether or not they would receive the OptiBIRTH intervention at that site. Hence, the primary analyses for the trial (see below) will consider data at the level of each site as a whole, rather than at the level of the women who were approached and formally recruited.

Within each of the three countries, the maternity units were matched by their annual number of births and then by VBAC rate. They were matched in either pairs or triplets and then randomised 1:1 or 2:1 to intervention or control, respectively. The randomisation was done using the random number generator in Microsoft Excel [RAND], with the first site in each matched pair or triplet being assigned a random number between 0 and 1. If the number was below 0.500, the site was allocated ‘OptiBIRTH intervention’. If it was above 0.500, the site was allocated ‘control’. If the number had been exactly 0.500 the randomisation would have been done again, but this did not happen. Where a matched pair had been formed, the second site was automatically allocated the opposite of the first site. Where a matched triplet had been formed, if the first site was allocated to the control group, the other two sites were automatically allocated to the intervention group. If the first site was allocated to the intervention group, the randomisation was repeated for the second site, and the third site was automatically allocated to the opposite of the allocation for the second site.

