### Outcome measures

#### Primary

The primary outcome measure will be the VBAC rates for women with one previous caesarean section for each site comparing the years before and after the delivery of the intervention. This is calculated as the number of women who gave birth by spontaneous vaginal delivery or with the use of ventouse or forceps after a single previous caesarean section, divided by the total number of women who gave birth at the site after a single previous caesarean section.

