### Sample size assumptions and estimates

The sample size for this cluster randomised trial was derived by adjusting an estimate for the sample size for an individually randomised trial to allow for clustering. This was done by inflating the estimate by the design effect given by 1 + (ñ-1)ρ, where ñ is the average cluster size and ρ is the estimated intra-class correlation coefficient (ICC) for this study. With a background proportion of successful VBAC of 25 % and an ICC of 0.05, 12 trial units would be required, each containing 120 participating women (840 women in the intervention group and 840 women in the control group), to detect a 15 percentage point difference in successful VBACs (that is, an increase from 25 % in the control group to 40 % in the intervention group), with power of at least 80 % and an alpha level of 0.05. If the true ICC values are less than 0.05, the power of the study will increase. To allow for a loss to follow-up of 20 % of women and the possibility that one site per country will drop out of the trial, 15 trial units (16 maternity sites) were randomised across three countries.

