## Discussion

Recruitment to the OptiBIRTH trial is expected to close in all sites in 2015, with all participating women expected to birth by the end of the year. Recruitment has been slower than anticipated, in part because birth rates have fallen at several of the sites. As with cluster randomised trials in general, it has not been possible to recruit all potentially eligible women at each site. Among the reasons for this are that some of the women who were offered participation in the trial did not wish to join and because of challenges in fully initiating the study in each site. This may introduce differences between the participants in the intervention and control sites, which reinforces the importance of the primary analyses being a comparison of the VBAC rates for all women with one previous caesarean section at each site before and after the study period using routine data from each site. If the OptiBIRTH intervention succeeds in increasing VBAC rates, its application across Europe might avoid 160,000 unnecessary caesarean sections every year, which occur at an extra direct annual cost of more than €150 million.

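### A randomised German site was withdrawn for recruiting nobody, although the primary outcome uses routine site-wide data; as written, the primary comparison has no way to include it

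*Protocol article*

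**What the plan says.** All references are to the protocol article.

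- **Timing.** Registration gives "randomisation conducted: 7 April 2013". The pilot began in January 2014 with sites already allocated (Pilot study).
- **What was randomised.** Sample size assumptions and estimates: "15 trial units (16 maternity sites) were randomised across three countries". The difference of one arises because "two maternity units in the same city in Germany were considered as a single cluster for the purposes of the trial" (Design).
- **The withdrawal.** Study setting begins with "A total of 16 sites (maternity units) agreed to take part in the OptiBIRTH trial initially" and then says "one of the German sites was withdrawn from the trial because of failure to recruit any participants in the first 6 months". It does not give that site's arm, the cause of its failure to recruit, or whether it was one of the two merged units.
- **Primary outcome.** The rate is births by vaginal route after a single previous caesarean, "divided by the total number of women who gave birth at the site after a single previous caesarean section". The Discussion describes the primary analysis as follows: "comparison of the VBAC rates for all women with one previous caesarean section at each site before and after the study period using routine data".
- **Why that level was chosen.** Randomisation: "it is possible that recruitment of women to the trial was influenced by the knowledge of whether or not they would receive the OptiBIRTH intervention". The section draws from this that the primary analyses should use each site as a whole.
- **What is compared, and when.** Data analysis compares the change in VBAC rate in the sites taking part, from calendar year 2012 to the 12 months after the month of the last trial baby's birth at each hospital. The fallback is the calendar year following that same birth.

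**The concern.** The protocol moves its primary analysis away from recruited women because recruitment, in an unblinded cluster trial, may differ by arm. Withdrawing a whole site because it recruited nobody brings recruitment back in through the choice of sites. If the site's routine counts are left out, the set analysed is no longer the set randomised, and whether a site is in it depends on something that happened after allocation. With 15 clusters, one site can move an arm mean noticeably. If the site was a cluster of its own, its matched pair or triplet is also left incomplete.

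**Working it through.** **1. Does the outcome need recruits?** Numerator and denominator are routine counts of births at the site. Neither uses a consent form. The site's 2012 rate and a later annual rate are defined whether or not any woman joined.

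**2. Does the written rule admit the site?** It fails in two places. The comparison covers sites taking part, and this one was withdrawn from the trial. The follow-up window, and its calendar-year fallback, are both dated from the last trial baby at that hospital, and there is none. Exclusion is not stated in so many words, but no written route leads to inclusion.

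**3. The plan's own dropout figure.** 12 units required + 1 per country × 3 countries = 15, which agrees with the 15 units randomised. Loss of a site was planned for in the sample size.

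**4. The allocation split.** Germany has six sites with two merged, so five clusters; Ireland and Italy have five each. Five clusters divide into pairs and triplets only as 2 + 3. At 1:1 and 2:1 that is 3 intervention and 2 control per country, so 9:6 overall.

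**5. Power on the protocol's inputs** (25% against 40%, ICC 0.05, 120 women per cluster).
- Design effect: 1 + (120 − 1) × 0.05 = 6.95.
- The stated 840 per group reproduces with one-sided alpha 0.05: 120 × 6.95 = 834, or 6.95 clusters, rounded to 7 × 120 = 840. Two-sided it would be 152 × 6.95 = 1,056. (Separately, 12 × 120 = 1,440, whereas 840 + 840 = 1,680 = 14 × 120.)
- Normal-approximation power by number of clusters, intervention:control:

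| Clusters | Two-sided | One-sided |
|---|---|---|
| 9:6 | 0.711 | 0.812 |
| 8:6 | 0.691 | 0.795 |
| 9:5 | 0.658 | 0.769 |

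The loss is about 2 points if an intervention cluster goes and 4 to 5 if a control cluster goes.

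**6. Power for the change-score comparison that the primary analysis makes.** Two inputs are not in the protocol and are assumed: 300 women per site-year, and a between-year correlation r of the site component. Write b = ICC × p(1 − p) and w = (1 − ICC) × p(1 − p)/300.
- At 25%: b₀ = 0.009375, w₀ = 0.000594. At 40%: b₁ = 0.012, w₁ = 0.00076.
- Control change variance: 2b₀(1 − r) + 2w₀ = 0.00681 at r = 0.7.
- Intervention change variance: b₀ + b₁ − 2r√(b₀b₁) + w₀ + w₁ = 0.00788 at r = 0.7.
- Standard error at 9:6: √(0.00788/9 + 0.00681/6) = 0.0448, so the noncentrality is 0.15/0.0448 = 3.35 on 13 df, two-sided t test.

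| r | 9:6 | 8:6 | 9:5 |
|---|---|---|---|
| 0.5 | 0.70 | 0.67 | 0.65 |
| 0.7 | 0.871 | 0.848 | 0.829 |
| 0.9 | 0.995 | 0.993 | 0.990 |

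The loss is 2 to 5 points at r = 0.5 to 0.7 and under 1 point at r = 0.9. The level of power depends mainly on the assumed r.

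**7. Possible shift in the estimate.** With sites weighted equally, dropping a site whose change differs by D from the mean of the rest of its arm moves that arm's mean by D/k, where k is the number of clusters in the arm. Taking D = 15 points, the size of the target effect, as an illustration: 15/9 = 1.7 points for an intervention site and 15/6 = 2.5 points for a control site. For example, eight intervention sites changing by 15 and one by 0 average 8 × 15/9 = 13.3; without that one the mean is 15.0. If only half of the merged cluster is lost, the shift is smaller. The sign depends on the arm and on the sign of D, and neither is known.

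**The case against.** The strongest reply has four parts.

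- **The SAP may settle it.** Handling of withdrawn clusters is ordinary SAP content, and the article defers detail to a SAP that is not shown. This stands in part: the SAP may already keep the site. But the article itself fixes which sites are compared and how the window is dated, and those rules shut the site out. That is more than a missing detail.
- **Dropout was allowed for.** This fully answers a complaint about power. It does not answer one about bias, because extra clusters do not correct a selective loss.
- **The reason may have nothing to do with allocation.** A reader might infer that the site was lost because of its allocation. The documents do not show that. The Randomisation remark is general, and the Discussion gives other reasons for slow or incomplete recruitment: falling birth rates, women declining, and difficulty in getting the study fully started. The text supports a possible relation to allocation, no more.
- **A whole cluster may not be lost.** If the site is one of the two merged German units, all 15 clusters and every matched set survive, one of them smaller.

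Two further inferences are tempting. One is that exclusion flatters the intervention. That needs the arm, and it needs non-recruitment to signal a poor change in VBAC rate. The protocol says clinician education and a community of practice should reach all women at a site, so having no recruits does not imply no effect. The other is that power falls further because the rest of the matched pair or triplet must go too. The article specifies no matched analysis, so nothing requires that.

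**Conclusion.** The point holds as one about bias and cluster-level intention-to-treat. A randomised site was withdrawn for a reason irrelevant to how the primary outcome is measured, and the article's rules leave no way to bring it into the primary comparison. What is at risk is one of 15 clusters, or part of one. The reason may be related to allocation; arm, cause, cluster status and direction of bias are not reported, and exclusion is implied rather than stated.

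Power is not the issue. The loss is roughly 2 to 5 points, or less than 1 if site rates are very stable between years. The change-score figures rest on an assumed 300 women per site-year and an assumed correlation. The illustrative shift of 1.7 to 2.5 points rests on an assumed 15-point difference and equal weighting of sites. This is a cheap improvement, worth making before the primary data are assembled.

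**What to change.** - State that withdrawal ends recruitment and the collection of woman-level data only.
- Report the withdrawn site's arm and whether it belongs to the merged cluster.
- Request its aggregate routine counts for 2012 and for the follow-up year, and analyse it in its allocated arm, and in its matched set if matching is used.
- Define a follow-up window that does not depend on a recruit, such as a common calendar year.
- Report the analysis without the site as a sensitivity analysis, and apply the same rule to any later site that recruits nobody.

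The cost is a request to one hospital for aggregate figures for two years and a short statement in the SAP. The article was submitted in May 2015 with recruitment still open, so the follow-up year could still be set. The downside is that the hospital may decline. In that case, say so, give its arm and cluster status, and bound the effect by letting its unknown change vary over a plausible range.

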## Methods/Design

### Design

This is a cluster randomised trial of maternity units in three countries with relatively low VBAC rates (Germany, Ireland and Italy). The units represent a variety of healthcare settings (small, medium and large units, with annual births of 2,000 to 8,500) in both urban and rural locations [14]. For the purposes of the randomisation, two maternity units in the same city in Germany were considered as a single cluster for the purposes of the trial.

